### Intervention

#### Structure

The intervention period will last for 6 months, with each intervention component delivered over a standardized two-month period (see Table 2). Participants will be allocated to one of the four study arms:First-arm (individual-level only):

**Table 2 tab2:** Intervention design.

Month	1				2				3				4				5				6			
Week	1	2	3	4	5	6	7	8	9	10	11	12	13	14	15	16	17	18	19	20	21	22	23	24
First-arm	**Individual-level only**																							
	Individual-level (Duration: once a week, 60 min per session, via telephone)								Individual-level maintenance (Duration: once a week, 15 min per session, via telephone)															
Second-arm	**Individual- + interpersonal-level**																							
	Individual-level (Duration: once a week, 60 min per session, via telephone)								Interpersonal-level (Duration: once a week, 60 min per session, via telephone)								Individual- + interpersonal-level maintenance (Duration: once a week, 15 min per session, via telephone)							
Third-arm	**Individual- + interpersonal- + community-level**																							
	Individual-level (Duration: once a week, 60 min per session, via telephone)								Interpersonal-level (Duration: once a week, 60 min per session, via telephone)								Community-level (Duration: once every 2 weeks, 2 h per session, in-person)							
Fourth-arm	**Education-only control group**																							
				X				X				X				X				X				X

X—monthly messages on healthy diet tips, recognizing warning signs of health, understanding dementia, fall prevention tips, health messages, and anti-fraud tips via text, graphics or voice recordings will be sent out.

Participants will receive the individual-level intervention for 2 months, comprising weekly 60-min telephone sessions. This is followed by 4 months of weekly 15-min maintenance sessions delivered via the telephone to reinforce key skills and ensure consistency in intervention duration across arms.Second-arm (individual- + interpersonal-level):

Participants will receive the individual-level intervention in the first 2 months followed by the interpersonal-level intervention in the next 2 months, each delivered as weekly 60-min telephone sessions. In the remaining 2 months, participants will receive weekly 15-min maintenance sessions delivered through telephone to consolidate learning from both components.Third-arm (individual- + interpersonal- + community-level):

Participants will receive the individual-level (2 months) and interpersonal-level (2 months) interventions as described above, followed by a community-level intervention (2 months) consisting of four in-person, community-led sessions (approximately 2 h each). No maintenance sessions will be provided in this arm to avoid overburden for participants.Forth-arm (education-only control):

Participants will receive SMS monthly messages via text, graphics (e.g., posters), or voice recordings for a period of six months.

All intervention sessions are delivered by trained volunteers, supervised by the research team. Volunteers are used because they enable scalable, cost-efficient delivery, and reflect real-world implementation conditions. Detailed session content for each component can be found in Supplementary Tables 1–3.

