Against this backdrop, the present study aims to address this gap by evaluating the incremental benefits of a multi-level interventions. Specifically, we examine whether augmenting an individual-level intervention with interpersonal and community components leads to greater and more sustained reduction in loneliness.

At the individual level, psychological interventions have shown promising results in reducing loneliness (24, 25). Mindfulness-based approaches foster present-moment awareness and emotional regulation (26, 27), while behavioral activation promotes engagement in meaningful and rewarding activities; both have shown effectiveness in alleviating loneliness (25, 28). In Hong Kong, these approaches were successfully adapted for telephone delivery by trained volunteers during the COVID-19 pandemic (29, 30, 96), although their effectiveness beyond pandemic remains uncertain. Meta-analyses further indicate that interventions combining cognitive behavioral therapy (CBT) with strategies to enhance social connection are among the most promising strategies for reducing loneliness (17, 19). CBT enables older adults to modify maladaptive thoughts and behaviors related to themselves and social situations (31). Supporting this, an RCT demonstrated that an eight-week internet-based CBT (ICBT) intervention incorporating functional behavioral model, cognitive restructuring, behavioral activation to increase social participation, and psychoeducation effectively reduced loneliness in adults (32). Drawing on this evidence, we will enhance our individual-level intervention by integrating a cognitive component adapted from the ICBT developed by Käll et al. (32), with a locally validated mindfulness-based intervention (29, 30, 96), delivered by trained volunteers via the telephone, a modality selected for its accessibility, low cost, and feasibility among older adults facing mobility, digital, or socioeconomic barriers.

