### Objectives

This primary objective of this study is to develop, implement, and evaluate a multi-level intervention comprising individual-, interpersonal-, and community-level components to reduce loneliness and enhance well-being among older adults in Hong Kong. The specific goals are to:

Evaluate the short-term effectiveness of the individual-level intervention, compared with an education-only control group in reducing loneliness.Assess the incremental benefit of adding an interpersonal-level intervention to the individual-level intervention in further reducing loneliness, compared with the individual-level intervention alone.Assess the incremental benefit of adding a community-level intervention to the combined individual- and interpersonal-level intervention in reducing loneliness.Examine potential mediators through which individual-, interpersonal-, and community-level interventions influence loneliness outcomes.Examine the long-term effects of the individual-level only, individual- + interpersonal-level; and individual- + interpersonal- + community-level interventions, compared with an education-only control group, on loneliness, physical and mental health, cognitive functioning, and healthcare utilization.Evaluate the cost-effectiveness of individual-level only, individual- + interpersonal-level; and individual- + interpersonal- + community-level interventions compared with education-only control group.

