#### Content

##### Individual-level

The individual-level intervention combines a mindfulness-based approach and cognitive behavioral therapy (CBT) principles. The mindfulness component is adapted from the smartphone-delivered intervention (27) and previously validated among older adults in Hong Kong (29, 30, 56, 96). The CBT component is adapted from SOLUS-D, an evidence-based interactive self-help programme designed to reduce loneliness (32, 57). Participants will receive eight weekly 60-min sessions delivered over the telephone by trained volunteers. Session content includes body awareness and present-moment awareness, emotional awareness and mind–body labelling, relaxation techniques and sensory discrimination, deepening awareness and accepting feelings, exploring intrinsic needs, understanding the interconnection between thought patterns and emotions, overcoming negative thinking, and cultivating a positive mindset. Brief maintenance sessions will reinforce intervention content through guided exercises and supporting videos.

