##### Interpersonal-level

The interpersonal-level intervention will adapt content from Group 4 Health (G4H), a psychosocial programme designed to strengthen social group identification and belonging (39). G4H will also be adapted for telephone delivery, while preserving its core theoretical mechanisms through structured reflection, guided exercises, and goal-settings. Participants will engage in eight weekly 60-min sessions delivered via telephone by trained volunteers. Sessions focus on understanding the benefits of social connections, exploring self and community, examining interpersonal networks in daily life, managing and improving interpersonal relationships, expanding social groups, and ongoing practice and review of social goals and resources. Maintenance sessions will reinforce the intervention content through guided practice and supporting materials.

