##### Community-level

The community-level intervention will adapt concepts from Neighbours Every Day, a community-based initiative that promotes neighbourhood cohesion through inclusive and socially engaging activities (43). Participants will attend four weekly 2-h in-person sessions over 2 months, held at accessible community venues. Each session will accommodate up to 42 participants, with structured subgroup activities (up to six participants) to encourage deeper engagement. The intervention aims to help participants build neighbourhood connections, get to know each other, strengthen mutual support, enhance community bonds, foster a sense of belonging, create a cohesive community, and establish trustworthy relationships. No maintenance is included to minimize participant burden as the intervention is designed to promote community engagement beyond formal sessions.

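### Objective 3 asks what adding the community level gains, but arm 3 receives it in place of arm 2's maintenance calls, so a null or small arm 3 versus arm 2 difference cannot be read as no community benefit

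*Protocol article*

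**What the plan says.** The third specific goal under Objectives reads: "Assess the incremental benefit of adding a community-level intervention to the combined individual- and interpersonal-level intervention in reducing loneliness". The Introduction puts the general question as whether augmenting the individual level with the other two "leads to greater and more sustained reduction in loneliness".

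Structure and Table 2 set out the delivery. Arms 2 and 3 both have eight weekly individual-level sessions (weeks 1-8) and then eight weekly interpersonal-level sessions (weeks 9-16), each of 60 minutes by telephone. They part in the last two months:

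- Arm 2: "participants will receive weekly 15-min maintenance sessions delivered through telephone to consolidate learning from both components".
- Arm 3: four in-person community sessions of about 2 h each. "No maintenance sessions will be provided in this arm to avoid overburden for participants".

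The Content section repeats the omission for the community level and gives a reason: "No maintenance is included to minimize participant burden as the intervention is designed to promote community engagement beyond formal sessions".

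The same section describes maintenance as active content. For the individual level: "Brief maintenance sessions will reinforce intervention content through guided exercises and supporting videos". For the interpersonal level: "Maintenance sessions will reinforce the intervention content through guided practice and supporting materials".

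**The concern.** An incremental benefit of adding a component is normally estimated by comparing two arms that differ only in that component. Arms 2 and 3 differ in two ways at once in weeks 17-24: arm 3 gains the community sessions and does not get the calls that arm 2 receives. The protocol describes those calls as reinforcing what was taught, so they cannot be treated as inert.

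At stake is the reading of a weak result. The Discussion aims to find the most effective and sustainable configuration. If arm 3 does no better than arm 2, the wording of Objective 3 invites the conclusion that the community level adds nothing, and it might then be dropped from later programmes. The same data would fit a community benefit that merely equals what continued calls achieved.

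**Working it through.** **Inputs** (Structure, Table 2, Content). Arm 2, weeks 17-24: one 15-minute call a week. Arm 3, weeks 17-24: four sessions of about 120 minutes and no maintenance sessions. Table 2 has the community sessions every two weeks and the Content section calls them weekly, but both give four, so the totals are unaffected.

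**Contact in weeks 17-24**

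| | Arm 2 | Arm 3 | Arm 3 minus arm 2 |
|---|---|---|---|
| Maintenance calls | 8 × 15 = 120 min | 0 | −120 min |
| Community sessions | 0 | 4 × 120 = 480 min | +480 min |
| Net | 120 min | 480 min | +360 min |

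**Time since last formal session on each earlier component, at the end of week 24**

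- Arm 3: individual level 24 − 8 = 16 weeks; interpersonal level 24 − 16 = 8 weeks.
- Arm 2: 24 − 24 = 0 weeks for both, since its calls cover both components through week 24.

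**What the contrast estimates.** Let E be the reduction in loneliness from the four shared months, C the further reduction from the community sessions as delivered, and M the further reduction from the eight calls. Under additivity:

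- arm 2 = E + M
- arm 3 = E + C
- arm 3 − arm 2 = (E + C) − (E + M) = C − M

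A pure addition would give C, either as (E + M + C) − (E + M) or as (E + C) − E. The trial has no arm with E + M + C and none with E alone.

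**Reading the result, for M ≥ 0**

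- M = 0: the contrast equals C and nothing is lost.
- 0 < M < C: the contrast is positive but smaller than C.
- M = C: the contrast is zero although the community sessions work.
- M > C: the contrast favours arm 2 even if C is positive.

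So C − M ≤ C, and a positive contrast implies C > 0. A contrast near zero does not show that C is near zero. The document gives no value for M, so the understatement in loneliness points cannot be computed and none is assumed here.

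**Can the analysis separate C from M?** The model under Planned statistical analysis has fixed effects for time, group (control as reference) and their interaction, with random intercepts for clusters. Arm 3 versus arm 2 is a difference between group-by-time terms. Within these two arms, the calls and the community sessions are each fully determined by arm in weeks 17-24, so no term can split them. The change in arm 2 from T2 to T3 does not recover M either, because it mixes the effect of the calls with any fading or delayed effect of the earlier sessions.

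**The case against.** The strongest reply is the package reading. The Abstract calls the trial pragmatic and the Discussion speaks of comparing intervention intensities and configurations. On that view arm 2 means arm 2 as laid out in Table 2, calls included, and the comparison answers a practical question: after four shared months, are community sessions better than brief calls? The omission is also deliberate, disclosed and explained twice by participant burden, and the Discussion flags fatigue in the more intensive arms. Adding calls to arm 3 would raise that burden. Removing them from arm 2 would widen the contact gap from 360 to 480 minutes.

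All of this justifies the delivery, and the package comparison is legitimate. It does not rescue the wording of Objective 3: if arm 2 is a package that includes its calls, arm 3 is still not that package plus the community level.

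It is also fair that nowhere does the protocol say a null difference will be read as no benefit, and that a non-significant result never proves absence of benefit. The ambiguity here is a separate one: even a precise estimate near zero would leave C undetermined.

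Two stronger readings may tempt a reader. One is that arm 3 has no reinforcement of the earlier components after week 16. The document shows only that it has no maintenance sessions. Detailed session content is in supplementary tables not shown here, and the visible content overlaps: interpersonal sessions work on widening social groups, and community sessions have people build ties with neighbours, which could be practice of the same skills. The other is that Objective 2 fails in the same way. Its comparator is arm 1, whose maintenance calls are openly part of the individual-level package, so extending the point there adds little.

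**Conclusion.** The point holds as a mismatch between Objective 3 and the arms, at low severity. Arm 3 minus arm 2 estimates community sessions (480 min, in person) versus continued brief maintenance (120 min, by telephone), not the addition of one level to an otherwise unchanged intervention.

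Under two assumptions, additive effects and a maintenance effect that is not harmful, the contrast is a lower bound for the effect of the community sessions as delivered, which includes the 360 minutes of extra contact. A positive difference then supports the community level. A null or small difference, including on whether any reduction is more sustained, cannot be read as no community benefit.

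A reader might infer that the trial is shown to be biased against the community level. The document does not support that, since the maintenance effect is not given and may be zero. Nor is there any problem for the comparisons of each arm with control, which remain valid as comparisons of whole packages.

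**What to change.** Restate Objective 3 as: *the effect of community-level sessions versus continued brief maintenance calls in months 5-6, after the individual and interpersonal levels*. Add one sentence: *a null or small difference between arm 3 and arm 2, including for more sustained reduction, will not be concluded as no benefit of the community level*.

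Leave the arms, delivery, sample size and comparisons with control unchanged. The cost is two edits to the text and a slightly narrower claim for Objective 3. Both are best made before outcome data are seen.

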#### Content

##### Individual-level

The individual-level intervention combines a mindfulness-based approach and cognitive behavioral therapy (CBT) principles. The mindfulness component is adapted from the smartphone-delivered intervention (27) and previously validated among older adults in Hong Kong (29, 30, 56, 96). The CBT component is adapted from SOLUS-D, an evidence-based interactive self-help programme designed to reduce loneliness (32, 57). Participants will receive eight weekly 60-min sessions delivered over the telephone by trained volunteers. Session content includes body awareness and present-moment awareness, emotional awareness and mind–body labelling, relaxation techniques and sensory discrimination, deepening awareness and accepting feelings, exploring intrinsic needs, understanding the interconnection between thought patterns and emotions, overcoming negative thinking, and cultivating a positive mindset. Brief maintenance sessions will reinforce intervention content through guided exercises and supporting videos.

##### Interpersonal-level

The interpersonal-level intervention will adapt content from Group 4 Health (G4H), a psychosocial programme designed to strengthen social group identification and belonging (39). G4H will also be adapted for telephone delivery, while preserving its core theoretical mechanisms through structured reflection, guided exercises, and goal-settings. Participants will engage in eight weekly 60-min sessions delivered via telephone by trained volunteers. Sessions focus on understanding the benefits of social connections, exploring self and community, examining interpersonal networks in daily life, managing and improving interpersonal relationships, expanding social groups, and ongoing practice and review of social goals and resources. Maintenance sessions will reinforce the intervention content through guided practice and supporting materials.

##### Community-level

The community-level intervention will adapt concepts from Neighbours Every Day, a community-based initiative that promotes neighbourhood cohesion through inclusive and socially engaging activities (43). Participants will attend four weekly 2-h in-person sessions over 2 months, held at accessible community venues. Each session will accommodate up to 42 participants, with structured subgroup activities (up to six participants) to encourage deeper engagement. The intervention aims to help participants build neighbourhood connections, get to know each other, strengthen mutual support, enhance community bonds, foster a sense of belonging, create a cohesive community, and establish trustworthy relationships. No maintenance is included to minimize participant burden as the intervention is designed to promote community engagement beyond formal sessions.

##### Education-only control

Participants in the education control group will receive monthly health-related SMS messages over a six-month period, serving as an attention control without introducing active psychosocial or therapeutic elements related to loneliness. Messages include topics such as healthy diet, fall prevention, dementia awareness, general health information, and anti-fraud tips. Therapeutic effects are minimized by avoiding content related to emotional regulation, social connection, or behavioral change techniques. For participants without smartphones, identical content will be delivered via email or postal mail.

#### Feasibility and retention strategies

To reduce fatigue and attrition, the intervention is delivered sequentially, with each level standardized to a two-month period. Telephone delivery of the individual- and interpersonal-level components aim to minimize mobility and scheduling barriers, with sessions arranged according to participants’ availability, with reminder calls provided by the research team. Based on prior experience (58), missed sessions are expected to be minimal. In the event if happens, sessions will be rescheduled within the intervention period and attendance will be documented. The community-level component is limited to four socially engaging, event-based sessions to reduce burden while promoting connection.

### Interventionists

All interventions will be delivered by trained volunteers, primarily retired individuals aged 50 to 70 years, who have completed at least 3 years of secondary education, report no significant physical or mental health issues or cognitive deficits, and are not employed full-time. Each eligible volunteer will be required to complete six weekly 2-h training sessions, led by trained social workers or mindfulness practitioners, depending on the intervention assigned. These sessions will include lectures, reading materials, and structured role plays to provide comprehensive preparation. Prior to intervention delivery, competency assessment will be conducted using observed role-play and standardized evaluation criteria (i.e., content delivery, protocol adherence). Each volunteer will deliver the intervention to one or two participants at a time, allowing for individualized attention and manageable workload. All volunteers will also receive a reimbursement in the form of supermarket vouchers.

#### Quality assurance

To ensure consistency in intervention delivery, standardized training materials, manuals, and recorded training sessions will be utilized. Ongoing supervision will be conducted weekly via group supervision meetings, monthly interventionists conferences, and continuous access to the research team for consultation. At least 20% of intervention sessions will be randomly selected for fidelity review using a structured intervention fidelity checklist documenting session duration, content coverage, participant engagement, and difficulties encountered.

Volunteers will also submit recordings of their initial sessions for review and feedback. Volunteers demonstrating difficulties or protocol deviations will receive targeted feedback, refresher training, or one-to-one supervision. Mid-project booster sessions will be conducted to reinforce competencies and adherence to intervention protocols. For the community-level intervention, an independent researcher will observe activities, document field notes, and report to the research team to ensure protocol adherence.

